### Design

We will pilot test the feasibility and acceptability of the intervention in a small RCT among 200 Latino/a MSM and TGW from Bienestar Human Services, Inc.’s (*Bienestar*) HIV testing sites. There will be approximately 90 MSM and 10 TGW in each arm. Participants will complete a survey at baseline, six, and 12 months. Participants will be randomized (procedures for this are described in detail below) into either the “information only” group (e.g. receiving text messages with HIV prevention information) or the “information plus” group (e.g. additionally receiving quiz questions that provide the possibility of winning prizes when answered correctly). Randomization will provide the comparison needed to identify the potential effect of winning a prize.

We will pilot the recruitment process with five participants. We will begin with a staggered enrollment process based on previous HIV testing data to identify the highest volume *Bienestar* sites. During the study we are collecting quantitative data on both primary outcomes (e.g. HIV knowledge and frequency of testing behavior) and secondary outcomes (e.g. HIV status).

All participating institutions received approval from their respective Institutional Review Boards and a certificate of confidentiality has been obtained from the National Institute of Mental Health. Any protocol modifications will be submitted to the IRBs for review, and participants will be informed if warranted. The trial was registered on 5 May 2017 with the ClinicalTrials.gov registry (NCT03144336).

### Setting

*Bienestar* is a community-based organization offering culturally tailored and linguistically appropriate programs and services to a predominately Latino population. Founded in 1989, *Bienestar* has seven locations in Los Angeles County. The populations served by *Bienestar* include people living with HIV and individuals at risk for HIV, gay and bisexual men, lesbian women, TGW, youth, and injection drug users. Three mobile testing vans provide HIV testing at the agency’s offices and in community venues. The agency provides linkage to HIV medical care for those testing HIV positive. Referrals are also provided to *Bienestar* prevention programs for HIV positive people and to outside agencies for services that *Bienestar* does not provide. *Bienestar* also offers individual-level and group-level interventions focused on reducing the risk of HIV infection or transmission; a syringe exchange program is available for injection drug users. Client services include mental health counseling, housing assistance, nutritional assistance via a food bank, treatment education, and a variety of support groups. *Bienestar* has an extensive history of implementing research, including NIH-funded collaborations with RAND (R01MH072351-05S, R34MH096544-01A1S1, R21DA035629) [21, 22].

### Characteristics of participants

Latino/a MSM and TGW clients who present at *Bienestar* HIV testing sites will undergo risk reduction counseling and rapid HIV testing following usual testing site protocols. Clients who test positive for HIV will be linked to services per the standard of care at *Bienestar*. Clients who test negative for HIV will be asked if they have interest in participating in the MOTIVES study. Those who express interest will be screened for the following eligibility criteria: own or have regular access to a smartphone; self-identify as MSM or TGW; self-identify as a Latino/a; aged ≥ 18 years; fluent in English or Spanish; able to provide contact information for at least three tracking mechanisms (e.g. cell phone, email, address, friend’s contact); and testing HIV negative.

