There are few published studies of using prizes for HIV-related behaviors; however, preliminary results from an ongoing study by the principal investigator (PI) [R34MH096609] to improve adherence using small lottery prizes in Uganda show promise. Over the first nine months of that study, individuals receiving incentives were nearly 25% more likely to achieve 90% antiretroviral adherence compared with the control group [19]. Taken together, these studies suggest further exploration of how lotteries support individuals in their effort to maintain their HIV-negative status.

In this pilot RCT, we focus on the local population of Los Angeles County, where Latino/a MSM and TGW are disproportionately impacted by HIV. The estimated HIV prevalence is 40% among Latino MSM [20] and 17% among Latina TGW [21]. MOTIVES—the **Mo**bile **T**echnology and **I**ncenti**ves** intervention—pilots a novel way to reach and support Latino/a MSM and TGW, who are hard to contact and have difficulty accessing relevant information about HIV prevention. We are pairing mobile technologies, a low-cost way to relay the most up-to-date prevention information, with incentives to encourage ongoing participation and translate key prevention messages into healthy behaviors. Our goal is to assess the feasibility and acceptability of the proposed intervention and associated outcome measures among potential participants and program staff to inform a definitive RCT on intervention effectiveness in the future.

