### MOTIVES intervention

Figure 1 details all stages of the MOTIVES intervention. Participants will be recruited by each tester after they complete their HIV test and the tester assesses that they may be eligible. Other HIV testers who are not part of MOTIVES are aware of the study and will be given flyers with the study information to provide to clients who might be eligible or interested. Eligible clients who express interest will participate in the consent process. Clients will receive a brief overview of the study and a description of the HIV prevention information and prize drawing components. The consent process will also make it clear that only half of the participants will be randomly assigned to the prize drawing group, but that all participants will receive the weekly information messages. Participants will also receive an additional consent document asking them to save the study phone number as “MOTIVES.” If they do not have a lock code on their phone, we will ask if they would like help in creating a code to increase privacy. The study team will confirm that the participants know how to delete messages if they have concerns about someone else reading their messages. The MOTIVES testers will give them information about when to expect text messages from the study (e.g. 2 pm on Thursday every week for one year and a reminder every 2.5 months to test again). The targeted testing frequency is at least once every three months. We will give participants examples of the kinds of text messages and quizzes they will receive and we will explain the odds of winning if they are in the intervention group. The hard copy of the signed consent form will be stored in a locked cabinet at each recruitment site. Following the consent process, the participant will be enrolled in the study by completing the Study Contact form that requires them to provide three tracking mechanisms and assigns them a Study ID number.

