In summary, the primary purposes of our pilot study are to demonstrate the acceptability and feasibility of methods proposed for a subsequent large-scale trial, to stabilize procedures so they are replicable, and to determine important parameters with sufficient accuracy to allow reliable estimates of sample size, power, and detectable effects for the subsequent study. “Mission-critical” parameters include proportions for dichotomous endpoints (such as agreeing to be enrolled in the trial, positive result by HIV rapid test); means and standard deviations for continuous endpoints (such as frequency of repeat HIV-negative test result); and the spectrum of response profiles for longitudinal studies (such as improvement or degradation in retention of HIV prevention information).

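### Eligibility ignores current testing frequency and entry follows an HIV test, so the testing parameters for the next trial may be diluted by clients already near the three-monthly target

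*Protocol article*

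**What the plan says.** Under Characteristics of participants, the article states "Those who express interest will be screened for the following eligibility criteria: own or have regular access to a smartphone". The list goes on to gender and sexual identity, Latino/a identity, adult age, fluency in English or Spanish, being "able to provide contact information for at least three tracking mechanisms", and a negative HIV test. No item refers to past or current testing frequency.

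Entry follows a test. The same section says "Clients who test negative for HIV will be asked if they have interest in participating in the MOTIVES study", and MOTIVES intervention says "Participants will be recruited by each tester after they complete their HIV test". Testers outside the study may also hand out flyers. Design adds that enrolment starts at the sites with the highest testing volume.

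On the behaviour to be changed, MOTIVES intervention says "The targeted testing frequency is at least once every three months". Testing frequency is one of two primary outcomes (Design; Data analysis; Table 1). Table 1 takes it from the clinic's own records. Data analysis treats it partly as a yes/no variable (tested within a three-month period) and partly as a continuous frequency. The closing paragraph of Data analysis gives as one purpose of the pilot "to determine important parameters with sufficient accuracy to allow reliable estimates of sample size, power, and detectable effects for the subsequent study".

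**The concern.** A client who already tests every three months can join and contributes to the testing means, standard deviations, proportions and arm difference that will size the next trial. On the three-month yes/no outcome such a client is already close to the maximum, so the observed difference is averaged over people with ample room to respond and people with little.

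Nothing stated in the article would reveal or handle this:

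- The review of the criteria in the acceptability and feasibility section looks at clients screened as ineligible and why. It cannot show how many clients already at target were admitted.
- The covariate adjustment in Data analysis is for characteristics found to differ between arms at baseline. A ceiling shared by both arms would not trigger it.

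At stake is the reading of the pilot. A small testing difference could mean a weak intervention or a sample partly at ceiling, and the planning figures would not tell the two apart.

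**Working it through.** **No figure to reproduce.** The only stated size is 200, and 2 × (90 + 10) = 200 agrees. The article gives no baseline testing distribution, so everything below rests on assumed testing rates and shows a range.

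**Inputs from the document.** Recruitment runs from 31 May 2017 to 9 May 2018 (Trial status): 343 days, or T = 343/365.25 = 0.94 year.

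**Assumed.** A share q of the clientele tests 4 times a year and the rest once a year.

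**Step 1: share of at-target clients among enrolees.** Three calculations bracket it.

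- Share of testing visits: 4q / (4q + 1 − q).
- Everyone presenting in the window enrolled once, regular visits: q / (q + (1 − q)T).
- Everyone presenting in the window enrolled once, Poisson visits: q(1 − e^(−4T)) / [q(1 − e^(−4T)) + (1 − q)(1 − e^(−T))].

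| q (assumed) | Visit share | Once-only, regular | Once-only, Poisson |
|---|---|---|---|
| 5% | 17% | 5% | 8% |
| 10% | 31% | 11% | 15% |
| 20% | 50% | 21% | 29% |

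For q = 20%: visits 0.8/1.6 = 50%; regular 0.2/(0.2 + 0.8 × 0.939) = 21.0%; Poisson 0.1953/(0.1953 + 0.4872) = 28.6%. If the others test twice a year, the three figures are 33.3%, 20.0% and 22.4%.

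A person enrols once, so the visit share is a limit. It is approached when only a small fraction of visits leads to enrolment. Clientele size is not given, so the position between the two cannot be fixed. As long as the remaining clients test less often, the enrolee share is not below q.

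**Step 2: effect of a fraction f with no response.** The arm difference shrinks by (1 − f), and the sample size for the same power grows by about 1/(1 − f)²:

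- f = 0.10: 1/0.81 = 1.23
- f = 0.20: 1/0.64 = 1.56
- f = 0.30: 1/0.49 = 2.04

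At the once-only figures for q = 20% (f = 0.210 and 0.286) this is 1.60 and 1.96.

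**Step 3: check with two proportions.** Assume that clients with room to improve move from 40% to 55% tested in a period and that ceiling clients stay at 95% in both arms. Two-sided alpha is 0.05 and power 80%.

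| f | Control | Intervention | Difference | n per arm | Ratio to f = 0 |
|---|---|---|---|---|---|
| 0 | 40.0% | 55.0% | 15.0 points | 173 | 1.00 |
| 0.10 | 45.5% | 59.0% | 13.5 points | 214 | 1.24 |
| 0.20 | 51.0% | 63.0% | 12.0 points | 267 | 1.54 |
| 0.30 | 56.5% | 67.0% | 10.5 points | 336 | 1.94 |
| 0.50 | 67.5% | 75.0% | 7.5 points | 571 | 3.30 |

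The ratios follow 1/(1 − f)² closely up to f = 0.30. At f = 0.50 the formula gives 4.0 against 3.30, because the binomial variance has fallen.

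**The case against.** Four objections carry weight.

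**Visits are not enrolees.** A reader might infer from recruitment at testing visits that quarterly testers are met four times as often and so fill half the sample when they are 20% of clients. The document does not support that. People enrol once, and over 343 days nearly all annual testers who keep a regular schedule also present. If all of them are enrolled, over-sampling is slight to moderate (21% to 29%). Vans in community venues (Setting) and high-volume sites say nothing about visits per client. This stands and limits the size. It does not remove the point, because dilution needs no over-sampling: f = 20% alone gives 1.56 times.

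**At target does not mean unable to respond.** The Abstract speaks of initiating and also sustaining change, the target is a minimum, and frequency is also analysed as a continuous quantity. A regular tester might be kept from declining or might test more often. This stands, so zero response is the extreme case.

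**The future trial is not said to be for under-testers.** The Background describes people "who are hard to contact and have difficulty accessing relevant information about HIV prevention", which concerns contact and information, not low testing. If the next trial recruits in the same way, the overall parameters are the right planning values for it. This stands, so below-target figures should sit beside the overall ones and not replace them.

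**Subgroup and covariate detail belongs in an analysis plan, which is not shown.** Partly fair: Data analysis does intend to look for subgroups that benefit. But the criteria, the point of recruitment, the adjustment rule and the way the criteria will be reviewed are all stated in the article, and as stated they leave clients already at target unseen.

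**Conclusion.** The point holds in a limited form. The criteria do not consider testing frequency and entry follows an HIV test, so clients already testing about every three months are eligible and have limited room to improve on the three-month outcome. Their share is undocumented and at least their share of the clientele, provided that the others test less often.

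The size is conditional. With an assumed 20% of clients testing quarterly and the rest annually, full once-only enrolment over the window gives 21% to 29% of enrolees. With no response in them, the implied sample size would be about 1.6 to 2.0 times larger. That is an upper bound for a given share, since any response in these clients reduces it.

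A reader might also infer that the comparison is biased. It is not: randomization spreads these clients over both arms, so the issue is dilution and interpretation. HIV knowledge, feasibility and acceptability are unaffected. The document contains no contradiction here. This is an inexpensive improvement to the planning value of the pilot, not a correction of an error.

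**What to change.** Leave eligibility and enrolment as they are, and make four changes:

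1. From the clinic records already used for the outcome, extract each enrolee's tests in the 12 months before enrolment and classify the enrolee as at or below the three-monthly target at entry.
2. Pre-specify prior testing frequency as a covariate in the testing models, whether or not it differs by arm.
3. Report the share already at target as part of the planned review of whether the criteria are suitable.
4. Report the testing parameters for the next trial (control-arm rate, standard deviation, arm difference with confidence interval) overall and separately for clients below and at target. Keep the overall estimate as the main one.

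The next trial can then choose its criteria and size with both sets of figures in view.

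The cost is one look-back field and some analysis wording. Subgroup intervals will be wider than the overall one. Clients new to the organization, or tested elsewhere before enrolment, may be misclassified as below target, so they should be flagged and the below-target results read with that in mind.

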### MOTIVES intervention

Figure 1 details all stages of the MOTIVES intervention. Participants will be recruited by each tester after they complete their HIV test and the tester assesses that they may be eligible. Other HIV testers who are not part of MOTIVES are aware of the study and will be given flyers with the study information to provide to clients who might be eligible or interested. Eligible clients who express interest will participate in the consent process. Clients will receive a brief overview of the study and a description of the HIV prevention information and prize drawing components. The consent process will also make it clear that only half of the participants will be randomly assigned to the prize drawing group, but that all participants will receive the weekly information messages. Participants will also receive an additional consent document asking them to save the study phone number as “MOTIVES.” If they do not have a lock code on their phone, we will ask if they would like help in creating a code to increase privacy. The study team will confirm that the participants know how to delete messages if they have concerns about someone else reading their messages. The MOTIVES testers will give them information about when to expect text messages from the study (e.g. 2 pm on Thursday every week for one year and a reminder every 2.5 months to test again). The targeted testing frequency is at least once every three months. We will give participants examples of the kinds of text messages and quizzes they will receive and we will explain the odds of winning if they are in the intervention group. The hard copy of the signed consent form will be stored in a locked cabinet at each recruitment site. Following the consent process, the participant will be enrolled in the study by completing the Study Contact form that requires them to provide three tracking mechanisms and assigns them a Study ID number.

At enrollment, we will take several steps to ensure the confidentiality of participants related to text message communication. For example, as mentioned above, MOTIVES HIV testers will instruct participants how to properly use the SMS system, maintain privacy on their device, and delete SMS messages from their mobile device. Finally, study staff will call the participant (either using an office line or using the *67 feature to make a protected call using their personal cell phone) to confirm that study staff has the correct cell phone contact number for the participant. At this time, participants will receive a $15 gift card.

After participating in the baseline survey and receiving their gift card, participants will be randomized using computer allocation by the study PI. The goal is to ensure that the randomization process does not influence responses to the baseline survey (e.g. responding more quickly if they were not chosen for the prize drawing group and feeling disappointed and less invested in the study). The study design was guided by its purpose as a pilot trial; we used a 1:1 randomization as it provides the greatest power for testing effectiveness in preparation for a future definitive RCT. Hereafter we will refer to the two groups as: (1) Information plus group (intervention group); and (2) Information only group (control group). HIV testers will also reaffirm that assignment is completely random and not based on the personal characteristics of any individual client. RAND study staff will explain to testers why randomization is so important, underscoring that only with their help can we actually understand if the intervention works. If testers select participants based on their own judgment of who is most in need of the intervention (e.g. they think a client appears particularly poor and would really appreciate having gift cards), we would not be able to collect accurate data. If a certain type of client is consistently included in the information plus reminders group, we will not be able to determine if the intervention works with everyone or just with a particular type of person.

Informed by findings from the focus groups during the formative phase, we created an incentive system where the chance of winning is high enough, yet not certain, and the prize amount is high enough, yet manageable for our budget. For each 12-week period in which a client is enrolled and has negative HIV test results, the client has a one out of 10 chance of winning a $50 gift card. Over the course of the year, if all four of a client’s HIV tests are negative, the client will have a four out of 10 chance of winning. If the client answered all of the quiz questions correctly, the client will approximately double the chance of winning.

Text messages that address the unique needs of Latino/a MSM and TGW clients will be sent weekly in Spanish or English, according to the participant’s preference. Based on feedback from our focus groups, we will send the initial information on Wednesday and a follow-up question on Friday. The text will include a link to additional information (e.g. CDC website with more information). The weekly information messages will have the following format: “*Hi this is MOTIVES, did you know that [information content]? Use this link [hyperlink] for more information*.” These messages are sent to both study groups. Because we asked participants to save the number from which we will send the messages as “MOTIVES,” they can easily recognize the sender without increasing the chance that study participation reveals their engagement with an HIV prevention exercise.

Messages will be sent once a week; two days later, only participants in the Information plus (i.e. prize drawing) group will receive a message with a question about the information (e.g. “*Is using two condoms safer than using one*?”). The answer option takes the format “*Press 1 if true, press 2 if false to increase your chances of winning a prize.*” This format has been found useful in the PI’s previous text messaging study as it avoids mistakes related to typos and reduces the effort and time needed to respond.

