As summarized in Table 1, we will explore a range of variables. The independent variables include control variables not only to improve efficiency, but also to learn about the paths through which the intervention works and to identify subgroups that are likely to particularly benefit from the intervention. Furthermore, potential mediators of behavior, such as level of acculturation, may result in improved provider communication and hence information access. For example, some people may want to avoid being seen at a clinic or HIV testing site, but for people who can communicate with providers more easily, this cost is close to zero, and their behavior may not be altered through the intervention. We can test this effect by forming an interaction between the acculturation measure and the intervention. With respect to the dependent variables, the primary outcomes include HIV knowledge and frequency of HIV testing; the secondary outcomes include HIV infection. Continuous variables will be assessed for normality and transformed if needed. Analyses will be conducted for the whole sample as well as for Latino/a MSM and TGW separately to arrive at the potentially differential impact of the MOTIVES intervention for these two groups. Logit estimation will be used for binary outcome measures.

We will impute missing data for some variables if an individual is still enrolled. When participants drop out, we will fit multiple logistic regression models to assess whether this dropout is random. If it is not, we will construct “non-response” weights using logistic regression that correct for dropout. Analyses will reflect these design effects in the calculation of standard errors and tests of significance.

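### Nothing in the described allocation secures the expected 10 transgender women per arm; a 13:7 or worse split would occur about one time in four, at modest cost

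*Protocol article*

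**What the plan says.** The Design section describes a "small RCT among 200 Latino/a MSM and TGW" and gives the make-up of the arms: "There will be approximately 90 MSM and 10 TGW in each arm". The same section points forward for the method: "Participants will be randomized (procedures for this are described in detail below").

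That description is in the MOTIVES intervention section. After the baseline survey, "participants will be randomized using computer allocation by the study PI". On the ratio, "we used a 1:1 randomization as it provides the greatest power for testing effectiveness". Testers are to reassure clients that "assignment is completely random and not based on the personal characteristics of any individual client". No section of the article mentions strata or blocks.

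The Data analysis section then plans subgroup work: "Analyses will be conducted for the whole sample as well as for Latino/a MSM and TGW separately", with the aim of seeing whether the effect differs between the two groups. For the overall comparison it plans ANCOVA, with a logistic counterpart for binary outcomes. The ANCOVA covariates are the client characteristics found to distinguish the arms at baseline.

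**The concern.** MSM/TGW status is an eligibility item, so it is known before anyone is allocated. The article treats the two groups as different enough to analyse separately, and one of them is expected to number only about 20. Yet the allocation as described does not use that status, so the TGW count in each arm is left to chance.

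Two things are at stake, both small. First, an uneven split widens the interval for the TGW comparison. Second, it leaves MSM/TGW unevenly spread over the arms in the overall comparison, and the covariate rule may not correct this because it acts only on an observed baseline difference.

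**Working it through.** **Inputs.** Total 200, about 90 MSM and 10 TGW per arm (Design); ratio 1:1 (MOTIVES intervention). TGW in total: 2 × 10 = 20.

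**The plan's own figure.** 2 × (90 + 10) = 200, and the expected number of TGW per arm is 20 × 0.5 = 10. The stated composition reproduces as an expectation.

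**Chance of an uneven split.** Let X be the number of TGW in one arm.

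- Coin-toss allocation: X ~ Binomial(20, 0.5), SD = √(20 × 0.5 × 0.5) = 2.24.
- Arms fixed at 100:100: X is hypergeometric (200 people, 20 TGW, 100 drawn), SD = √(100 × 0.1 × 0.9 × 100/199) = 2.13.

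| Split among 20 TGW | Coin toss | Arms fixed at 100:100 |
|---|---|---|
| exactly 10:10 | 17.6% | 18.6% |
| 12:8 or worse | 50.3% | 48.0% |
| 13:7 or worse | 26.3% | 23.8% |
| 14:6 or worse | 11.5% | 9.7% |
| 15:5 or worse | 4.1% | 3.2% |

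Permuted blocks that ignore MSM/TGW do not help. In simulation (20,000 runs for each block size from 2 to 20) the chance of 13:7 or worse was 23.5% to 24.2%. Because 20 is approximate, the coin-toss chance of a difference of six or more between arms was also computed for other totals: 21% with 16 TGW, 24% with 18, 29% with 22 and 31% with 24.

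**Cost within the TGW comparison.** For a difference in means with a common SD, the variance is proportional to 1/a + 1/b. Relative to 10:10, the ratio is (1/a + 1/b)/(1/10 + 1/10) = 100/(a × b) when a + b = 20.

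- 13:7: 100/91 = 1.10, so the SE is 4.8% larger.
- 14:6: 100/84 = 1.19, so the SE is 9.1% larger.
- 15:5: 100/75 = 1.33, so the SE is 15.5% larger.
- Averaged over the hypergeometric distribution: 1.05.

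For scale, the SE at 10:10 is √0.2 = 0.45 SD and at 13:7 it is 0.47 SD. Assuming 80% power and two-sided 5% (neither is stated in the article), the detectable TGW difference is 1.25 SD at 10:10 and 1.31 SD at 13:7.

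**Would the covariate rule pick it up?** The article gives no criterion for a baseline difference. Assume a chi-square test at 5%, without continuity correction. The pooled proportion is 20/200 = 0.10, and the SE of the difference is √(0.1 × 0.9 × 2/100) = 0.0424.

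- 13 v 7 per 100: z = 0.06/0.0424 = 1.41, p = 0.16.
- 14 v 6 per 100: z = 0.08/0.0424 = 1.89, p = 0.06.

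Under that assumption neither imbalance would bring MSM/TGW into the model.

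**Size in the overall comparison.** Assume, for illustration, that MSM and TGW differ by 0.5 SD on the outcome. A 13:7 split then shifts the unadjusted arm difference by 0.06 × 0.5 = 0.03 SD, against an SE of √(2/100) = 0.14 SD.

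**The case against.** The strongest reply is that this is an article. Strata and block sizes are commonly left to the full protocol, and the article refers to a final protocol version dated 12 November 2017. The statement that assignment ignores personal characteristics is a reassurance from testers about not picking favourites, and stratified allocation is also random within strata. This stands in part: a reader might infer that allocation was certainly unstratified, and the article does not prove that. But it does promise the procedures in detail, and the detail given contains nothing on MSM/TGW.

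The composition is also qualified as approximate, and an SD of about 2 around 10 fits that word. A reader might infer that the figure of 10 per arm is wrong. It is not; it is simply not secured.

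A reader might further infer that a subgroup of 20 cannot survive a chance split. The figures do not support that. The average variance inflation is about 5%, and it is the subgroup's size, much more than its split, that makes the TGW estimate weak.

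A similar case might be made for balancing by site, since "We will begin with a staggered enrollment process based on previous HIV testing data to identify the highest volume" testing sites. The documents give nothing from which to size a site effect. Testers read out only the baseline survey, which is finished before allocation, and the text messages are sent centrally. Site blocking is therefore not part of this point.

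Finally, covariate adjustment is already planned, and the separate analyses cannot be confounded by MSM/TGW. Both are true. The adjustment, however, depends on an observed difference, and the working shows splits it could miss. The primary aim, acceptability and feasibility, is little affected.

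**Conclusion.** The point holds as a minor one. The expected balance of 10 TGW per arm is not secured by anything in the described allocation. The chance of 13:7 or worse is about one in four under any scheme that does not stratify or minimise on MSM/TGW. The price is about 10% in TGW variance at 13:7, 19% at 14:6 and 5% on average. The overall comparison would be shifted only slightly, by 0.03 SD at 13:7 under the illustrative 0.5 SD gap.

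This rests on 20 TGW in total and on the article's description being complete with respect to MSM/TGW. The remark on the covariate rule also rests on an assumed 5% screening level. The point is worth acting on because the remedy costs almost nothing and because the pilot is meant to inform the design of a definitive trial.

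**What to change.** 1. Stratify the computer allocation by MSM/TGW, using concealed permuted blocks of varying size, with TGW as one stratum across all sites. If enrolment is under way, apply this to the remaining allocations. The article gives enrolment through 9 May 2018, so few or none may remain; in that case carry the stratification into the definitive trial.
2. In all cases, prespecify MSM/TGW as a fixed covariate in the overall ANCOVA and logistic models, in place of selecting it by observed baseline difference.
3. Report the realised TGW split by arm.
4. If the full protocol already stratifies by MSM/TGW, say so in one sentence and keep the fixed covariate.

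The cost is two allocation lists instead of one and one extra model term. No additional participants or staff are needed. Blocking makes late assignments in a block slightly more predictable; concealment and varying block sizes limit this.
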